
### Adverse Events

A safety questionnaire will be administered to all participants prior to the administration of the first rTMS in order to reduce the occurrence of risk. Possible symptoms, including seizures, tingling, burning sensations, headaches, pain at the electrode site, drowsiness, transient hearing changes, and transient acute hypomania induction (32), will be recorded at the end of each session. Although no adverse effects were found in the published trials on cognitive training reviewed by the committee, and there is little evidence of negative effects of cognitive training. However, any adverse events and negative reactions will be recorded. Descriptive statistics will be performed for all adverse events.

#### Potential Pitfalls and Contingency Plans

Adverse events attributable to rTMS may include seizures, headache, transient hearing changes, or irritability. The following measures will be taken to prevent these events: (a) patients will be enrolled in a detailed family search and review the medical history to confirm whether the patient has epilepsy, and if it occurs, exclude the patient from the group; (b) an adequate communication will be conducted by the investigator before the intervention to ensure that the patient is in a good position; (c) during the intervention, using Earplugs to minimize hearing damage; (d) the investigator will be closely aware of the patient's status and keep a record; (e) if the patient feels any discomfort, the intervention will be stopped immediately. Subjects may experience irritability and discomfort during MRI scanning. Methods to prevent these adverse events are as follows: check whether there is metal in the patient's body before enrollment, use anti-dry headphones to reduce sound stimulation during the examination; family members can accompany the examination if necessary. If irritation occurs, stop the scan immediately.

### Data Collection and Management

The trial process will be recorded via audio or in a written form to assure the authenticity of the intervention. A case report form (CRF) will be used to collect data. Two data managers will enter the data from the CRF into computer databases and will cross-check the uniformity of the hardcopy and electronic data. During the enrollment phase, each participant will remain anonymous through an assigned identifier. Only the CRF will record the patient's identifying information. All data are confidential to anyone external to the study with the exception of the ethics committee. Experimental data will be used to write clinical research articles. Experimental data will be used to write clinical research articles. Regarding the MRI data, we will obtain consent from the participants to keep the data in the hospital for future studies. During the process of the study, if participants discontinue or deviate from the intervention protocol, we will collect as much data as possible for further analysis.

We will use the following methods to facilitate participants' completion of the trial and follow-up: (a) enhancing communication between investigators and patients to gain patients' cooperation to the extent possible; (b) providing financial compensation according to the number of patients' study visits in order to encourage patients to continue to participate in the trial; and (c) providing free relevant examination results to study patients, including the results of cognitive assessments.

### Statistical Analysis

Baseline comparisons were used to examine potential differences between real-rTMS, sham-rTMS, and cognitive training, which ensured that there are no differences between the three groups. Potential baseline differences between the three groups will be detected. Gender, education, and pathological characteristics (axonal injury or cerebral hemorrhage) will be measured using Chi-square tests. The One-way ANOVA is conducted to analyze the outcome and information of the pre-intervention assessment. The Kolmogorov-Smirnov test will be used to evaluate the normality of distributions. If a normal distribution is confirmed, data will be presented as means and standard deviations (SD) and ANOVA will be used to analyze the effects at T1, T2, T3, and T4, with Bonferroni correction for multiple comparisons as a *post hoc* test. if it does not conform to a normal distribution, it will be tested using Kruskal-Wallis (non-parametric test). *P*-values <0.05 will be considered statistically significant. Data will be analyzed using the Statistical Package for Social Sciences (SPSS) software (v.22.0; SPSS, Inc., Chicago, IL, USA). MRI data will be examined in statistical parametric mapping using independent Student's *t*-tests. The statistical significance is P <0.001. To find other correlated factors that may have an impact on the efficacy of the intervention, correlations between changes in MRI data and changes in behavioral data will be calculated. Only patients completing the rTMS protocol will be included in analyses.

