## Introduction

The Centers for Disease Control and Prevention (CDC) defines a traumatic brain injury (TBI) as a mechanical injury to the brain caused by a collision, blow, or bump (1). TBI is a major health problem worldwide owing to the complex complications and sequelae associated with this condition. TBI affects more than 50 million people worldwide each year, including approximately 1.7 million people in the United States alone (2, 3). Although effective treatment in the acute phase has greatly improved survival among TBI patients, an estimated 5–7 million TBI patients in Europe and the United States suffer from multiple complications.

Cognitive impairment is the main clinical symptom of TBI. Cognitive impairment following TBI is often characterized by attention deficits, memory loss, and decreased executive ability. TBI can initiate a long-term neurodegenerative process that leads to pathological features similar to those of Alzheimer's disease (AD) (4–6). More than 50% of TBI patients experienced an impaired state of consciousness (i.e., a coma or a vegetative state), which has reported to persist in the form of long-term cognitive impairment (7). It is well known that deficits in executive function and memory are commonly detected within TBI, and these deficits are more difficult to treat as compared with deficits associated with other cognitive disorders as a result of the vulnerability of the affected brain regions (such as the frontal and temporal lobes). These sequalae negatively affect patients' quality of life as well as their rehabilitation process (8). Numerous studies have demonstrated that cognitive training can improve multiple cognitive domains inTBI involving reasoning, goal management, attention, as well as reorganized modular networks (9–11).

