Therefore, the proposed study aims to examine HF and LF, bilateral rTMS for the cognitive dysfunction in patients with TBI. In addition, magnetic resonance imaging (MRI) will be utilized to explore the association between brain structure and functional connectivity, as well as the cognitive effects of rTMS. The preliminary hypotheses of our study are (1) 4 weeks of bilateral high- and low-frequency rTMS is more effective in improving cognitive function in patients with TBI than sham stimulation and cognitive training and (2) structure MRI markers and functional connectivity pre- and post-intervention will be observed.

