### Sample Size Estimation

Sample size calculations were based on non-inferiority tests, as the purpose of this study was to show that the rTMS intervention was not inferior to cognitive training. According to studies showing that the effect size of working memory training on MCI is 0.74 and executive function is 0.575, we calculated the sample size using PASS 15 (effect size is 0.7, α is 0.05, power is 0.9). sample sizes of *n* = 10, *n* = 10, and *n* = 10 are obtained for the three groups. Moreover, two additional patients will be added to each group to compensate for possible dropouts. A total of 12 patients will be allocated to each group.

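### No stated contrast decides whether rTMS beats both sham and cognitive training: the Kruskal-Wallis branch is omnibus only, and the ANOVA branch loses power for that claim

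*Protocol article*

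**What the plan says.** In the Introduction, hypothesis 1 is directional and has two parts: four weeks of bilateral rTMS "is more effective in improving cognitive function in patients with TBI than sham stimulation and cognitive training".

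The Statistical Analysis section makes the test depend on a normality check. For normal data, "ANOVA will be used to analyze the effects at T1, T2, T3, and T4, with Bonferroni correction for multiple comparisons" as a post hoc test. For non-normal data, "if it does not conform to a normal distribution, it will be tested using Kruskal-Wallis (non-parametric test". The threshold is common to both: P-"values <0.05 will be considered statistically significant". The ANOVA factor is not named (group at each visit, or group and time), nor is the Bonferroni family or the visit that decides the hypothesis.

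Two other places bear on this. The Introduction says that "cognitive training can improve multiple cognitive domains" in TBI, so the authors expect the comparator to work. Sample Size Estimation cites studies in which "the effect size of working memory training on MCI is 0.74 and executive function is 0.575", plans 10 per group plus 2 for dropout, and gives non-inferiority of rTMS to cognitive training as the purpose. Only patients who complete the rTMS protocol are analysed.

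**The concern.** A three-group omnibus test has the null that all arms are equal. The null of hypothesis 1 is different: rTMS is no better than at least one of the two comparators. The two part company as soon as training beats sham. The omnibus null is then false whatever rTMS does, and a small P says neither which arm differs nor in which direction.

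The ANOVA branch has a second step that can locate the difference. The Kruskal-Wallis branch has none, so its only stated result cannot answer hypothesis 1. That branch may well be used, because the STT is scored as a completion time and such times can be skewed.

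In the ANOVA branch the question is efficiency. Hypothesis 1 needs both rTMS comparisons to succeed, and a claim that requires both needs no correction across the two. Bonferroni over all three pairs would charge it for sham v training, which hypothesis 1 does not concern. With 36 patients that charge is large.

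**Working it through.** **Inputs.** Arms 1:1:1; 10 evaluable or 12 randomised per arm (Sample Size Estimation); alpha 0.05 (Statistical Analysis); training effect 0.575 to 0.74 (Sample Size Estimation). Assumptions: the effects are in SD units against sham, outcomes have equal variance, the test compares groups at one time point, and Bonferroni covers the three group pairs. Higher is scored as better (STT time reversed).

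**The plan's own figure.** The 10 per group reproduces as an omnibus F test with Cohen's f = 0.7: noncentrality 30 × 0.7² = 14.7 gives power 0.911, while 9 per group (27 × 0.49 = 13.23) gives 0.873. It does not reproduce as a non-inferiority test with margin 0.7 SD and no true difference, which needs 35 per arm at one-sided 0.05. One arm differing by 0.7 SD is only f = 0.7 × √2/3 = 0.33.

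**Step 1: omnibus rejection when only training works.** For means (rTMS, sham, training) = (0, 0, d), the F test has noncentrality n × d² × 2/3 on 2 and 3n − 3 degrees of freedom. Example: n = 10, d = 0.74 gives 10 × 0.5476 × 2/3 = 3.65 and rejection in 34.7%. Kruskal-Wallis rates are simulated with normal data.

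| n per arm | d | ANOVA omnibus | Kruskal-Wallis |
|---|---|---|---|
| 10 | 0.575 | 22.3% | 20% |
| 10 | 0.74 | 34.7% | 32% |
| 12 | 0.575 | 26.5% | 25% |
| 12 | 0.74 | 41.5% | 39% |

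If rTMS equals training and both are 0.74 SD better than sham, hypothesis 1 is again false, and the rates are the same as in the d = 0.74 rows. With skewed data (lognormal, log-SD 0.6, an assumption) and only training working, Kruskal-Wallis rejects in about 36-52% at n = 10 and 43-61% at n = 12.

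**Step 2: what the ANOVA post hoc does in that setting.** With rTMS equal to sham and training better, Bonferroni over three pairs declares rTMS better than sham in about 0.8% of trials. Kruskal-Wallis followed by Bonferroni-adjusted Dunn comparisons would give about 0.6%, but the plan does not state that step.

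**Step 3: power to show superiority to both, means (d, 0, 0).** Written route: omnibus P < 0.05 and both rTMS pairs significant at 0.05/3 two-sided (critical t 2.55 at n = 10, 2.52 at n = 12). Alternative: both rTMS contrasts significant at two-sided 0.05 (critical t 2.05 and 2.03), using the pooled SD.

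| n per arm | d | Written route | Two planned contrasts |
|---|---|---|---|
| 10 | 0.7 | 8% | 18% |
| 12 | 0.7 | 10-11% | 23% |
| 10 | 1.0 | 24% | 42% |
| 12 | 1.0 | 32% | 51-52% |

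**Step 4: error of the alternative.** When rTMS equals training (both 0.74 SD better than sham), the two-contrast rule falsely claims superiority to both in 2.1-2.3% of trials. The bound is 2.5%, at a single time point.

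**The case against.** A reader might infer that the trial has a false-positive rate of 25-42%. The documents do not support that. When training beats sham the all-equal null is false, so rejecting it is correct, and no section says that an omnibus P will be reported as efficacy of rTMS. The upper end is also an ANOVA figure at 12 per arm, and in that branch the plan goes on to pairwise comparisons; the plan expects 10 evaluable. What stands is narrower: in the Kruskal-Wallis branch the omnibus P is the only stated result.

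The Step 1 rates are conditional on entering that branch, and how often this happens is unknown. Assuming lognormal times with log-SD 0.4 to 0.6, a Kolmogorov-Smirnov test with Lilliefors critical values rejects normality in 40-69% of trials when applied to all 36 values and in 15-28% when applied to one arm of 12. The Abstract describes the primary outcome as a change, for which skewness of raw times need not carry over.

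A follow-up to Kruskal-Wallis could be left to an analysis plan that is not shown. That would answer a bare omission. Here, however, the article gives a post hoc step in one branch and none in the other, and names the deciding contrast in neither.

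Bonferroni over all pairs is a common conservative choice, and the family is not stated, so the power comparison depends on that reading. It is an efficiency point, not an error. Finally, Sample Size Estimation gives non-inferiority to training as the purpose, so superiority to both cannot be treated as the trial's only aim without settling that conflict.

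**Conclusion.** The concern holds in limited form. Hypothesis 1 needs two directed rTMS comparisons, and the analysis text does not make either of them decisive.

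- **Kruskal-Wallis branch:** a significant result may be due to training alone, in about 20-32% of trials at 10 per arm or 25-39% at 12. This assumes normal data, rTMS equal to sham, and training 0.575-0.74 SD better than sham. The last is an assumption because the cited effects come from MCI with no stated comparator.
- **ANOVA branch:** false rTMS-over-sham claims stay under 1%. The cost is power, roughly halved at d = 0.7 (8% v 18% at 10 per arm) and cut from 42% to 24% at d = 1.0, if Bonferroni runs over all three pairs.

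This should be changed, but it does not show that the plan's error control has failed. Nor do planned contrasts make the trial well powered: at d = 0.7 they reach only 18-23%.

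**What to change.** In the Statistical Analysis section, test hypothesis 1 by two planned contrasts on the STT at one prespecified time point: real rTMS v sham, and real rTMS v cognitive training. Claim the hypothesis only if both favour rTMS, each at two-sided 0.05. If each comparison is to be claimed separately, use Holm over the two.

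Use the same two contrasts in the non-normal branch, as rank-sum tests with Hodges-Lehmann estimates and confidence intervals. Report the omnibus test as supportive.

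Reconcile this with the non-inferiority purpose in Sample Size Estimation. If that purpose is kept, sham v training stays a reported comparison, because it shows whether the comparator worked.

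The cost is wording only, with no extra patients or data. The downside is that, under the superiority hypothesis, sham v training loses confirmatory status.

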## Materials and Methods

### Study Design

The study is a prospective randomized placebo controlled, parallel-group trial that will be conducted at the Affiliated Hospital and the Second Clinical Medical College of North Sichuan Medical University. The protocol has been registered with the China Clinical Trial Registry (item number: ChiCTR2100050753). Our study will show improvement in cognitive function in patients with TBI following rTMS bilateral DLPFC intervention. The findings may provide a rationale for an approach of rTMS intervention for cognitive function in patients with TBI. Thirty-six patients with TBI will be enrolled in the trial. The physicians will provide patients with detailed information about the trial in verbal and written form before the trial begins.All patients will voluntarily sign an informed consent form. All patients will be screened according to eligibility criteria. 36 subjects will be randomized in a 1:1:1 ratio into the real-rTMS group, the Cognitive training group and the sham-rTMS group. All subjects will be required to perform neuropsychological assessments at before intervention, post-10 sessions, post-20 sessions, and 30 days after the intervention. MRI will be performed at pre-intervention and post-20 sessions. All patients will receive intervention for 4 weeks (30 minutes per day, 5 days per week). The diagram and schedule for the study are shown in Figure 1 and Table 1.

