#### Rs-fMRI Data Analysis

Resting-state fMRI images will be preprocessed and regional homogeneity (ReHo) analyses will be performed using DPARSF (Data Processing Assistant for Resting-State fMRI), REST (Resting-State fMRI Data Analysis Toolkit), and SPM8 (Statistical Parametric Mapping) software. Matrix Lab (Matlab2012b; MathWorks, Natick, MA, USA) has been chosen as the platform for data processing. In consideration the time required for participants to adapt to the scanning environment, we will remove the first ten time points from each subject's blood oxygen level dependent (BOLD) sequence; the remaining 230 time points will be subjected to time series corrections, head movement corrections, and head movement parameter tests. If the participants' head movement angle is **>** 2.00 at any angle of x, y, or z or if the maximum translational head movement is **>** 2.0 mm, the participant's data will be rejected. Next, the data space for each participant will be normalized to the Montreal Neurological Institute (MNI) standard space with resampled voxels of 3 × 3 × 3 mm. Six head movement parameters, mean white matter signals, mean whole brain signals, and mean cerebrospinal fluid signals will be removed as covariates and then subjected to de-linearization drift and filtering processing (0.01–0.08 Hz) to eliminate high frequency noise, such as from respiration and heartbeats. Based on the above processed data (i.e., for the ReHo analysis), the ReHo value of each voxel, termed Kendall's coefficient, will be obtained by calculating the consistency of the time series of each voxel and its surrounding adjacent 26 voxels. The ReHo value for each voxel of the whole brain comprises a complete ReHo map. For normalization, the ReHo map of each individual is divided by the average ReHo value of the whole brain. The final obtained image will then be smoothed with full width at half maximum (FWHM) = 4 × 4 × 4 mm. Post-processing of ALFF will likewise be analyzed using REST software. After combining the six cephalomotor parameters, the mean white matter signals, the mean whole brain signals, and the mean cerebrospinal fluid signals will be de-linearized and filtered (0.01–0.08 Hz) before being removed as covariates. After that, the filtered time series will be transformed to the frequency domain range via Fourier transform and a power spectrum at 0.01–0.08 Hz will be calculated. The square root of the power spectrum will be designated as the ALFF value. Each voxel-split ALFF value is divided by the mean value of all voxel ALFFs in order to obtain normalized mean ALFF values. Finally, all covariates will be removed. Functional connectivity analyses will be performed using ALFF with the brain regions of intergroup differences obtained by the ReHo method as seed points in order to assess whole-brain functional connectivity via gray matter templates.

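### Significance for whole-brain ReHo and ALFF maps is set at P<0.001 per voxel with no stated multiplicity correction, and the ReHo regions found this way seed the connectivity analysis

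*Protocol article*

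**What the plan says.** All statements are in the protocol article.

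- **Test and threshold (Statistical Analysis):** "MRI data will be examined in statistical parametric mapping using independent Student's" t-tests. The next sentence reads "The statistical significance is P <0.001".
- **Search space (Rs-fMRI Data Analysis):** data are normalised to standard space with "resampled voxels of 3 × 3 × 3 mm", and "The ReHo value for each voxel of the whole brain comprises a complete ReHo map". ALFF is likewise computed voxel by voxel. The ReHo map is smoothed at 4 mm FWHM.
- **Next step (Rs-fMRI Data Analysis):** connectivity is analysed "with the brain regions of intergroup differences obtained by the ReHo method as seed points".
- **Design (Study Design):** "36 subjects will be randomized in a 1:1:1 ratio into the real-rTMS group, the Cognitive training group and the sham-rTMS group". Also, "MRI will be performed at pre-intervention and post-20 sessions".
- **The only multiplicity correction in the article (Statistical Analysis):** "with Bonferroni correction for multiple comparisons". It is the post hoc step of the ANOVA of effects at T1 to T4 and is not attached to the imaging tests.

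The article does not say which pair of arms each t-test compares, or whether the tests use post-intervention maps or pre-to-post change maps.

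**The concern.** A threshold of P<0.001 is strict for one test, but here it is applied to tens of thousands of voxels. With no family-wise or cluster rule beside it, it does not limit the chance of a false finding anywhere in the brain. Maps would be expected to show significant voxels even if the stimulation had no effect on brain activity.

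The consequence does not stop at the first map. Regions that cross the threshold on ReHo are carried forward as seeds for a second whole-brain search in the same patients, so a seed may itself be a chance finding.

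What is at stake is the trial's imaging evidence. MRI markers and connectivity are the second hypothesis at the end of the Introduction, and Table 1 lists brain connectivity under secondary outcomes. Under the rule as written, significant voxels could not tell an effect from no effect.

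**Working it through.** The article states no voxel count, imaging error rate or imaging power, so there is no figure of its own to reproduce.

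**Inputs from the article:** voxel edge 3 mm, so volume 3 × 3 × 3 = 27 mm³; threshold 0.001; three arms; 12 patients per arm, or 10 after the dropout allowance (Sample Size Estimation).

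**Assumptions:** search volume 1.2 to 1.8 L; effective smoothness 4, 8 or 12 mm FWHM; two-sided tests (the article does not give sidedness).

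**1. Number of voxels** = search volume / 27 mm³.
- 1,200,000 / 27 = 44,444
- 1,800,000 / 27 = 66,667

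**2. Expected false-positive voxels per null map** = voxels × 0.001. This holds whatever the spatial correlation.
- 44,444 × 0.001 = 44
- 66,667 × 0.001 = 67
- If all three pairwise arm contrasts are run on one metric: 3 × 44.4 = 133 to 3 × 66.7 = 200.

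**3. Chance of at least one false-positive voxel.** For m effective independent tests it is 1 − (1 − 0.001)^m.

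| m | chance |
|---|---|
| 50 | 4.9% |
| 500 | 39% |
| 1,000 | 63% |
| 5,000 | 99% |

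Because neighbouring voxels are correlated, the effective m is below the voxel count. This was therefore checked by simulation.

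**4. Null simulation.** Volume of 38³ = 54,872 voxels (54,872 × 27 mm³ = 1.48 L), independent t-test, two-sided p<0.001, 60 maps per setting.

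| Smoothness (FWHM) | n per arm | Mean false-positive voxels | Maps with any | Median largest cluster (voxels) | Maps with a cluster of 10 or more |
|---|---|---|---|---|---|
| 4 mm | 10 | 55 | 60/60 | 2 | 0% |
| 4 mm | 12 | 57 | 60/60 | 2 | 0% |
| 8 mm | 10 | 54 | 60/60 | 7 | 23% |
| 8 mm | 12 | 53 | 60/60 | 8 | 23% |
| 12 mm | 10 | 60 | 60/60 | 15 | 77% |
| 12 mm | 12 | 61 | 60/60 | 16 | 83% |

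The mean counts are close to the expected 54,872 × 0.001 = 55. With 60 of 60 maps affected, the one-sided 95% lower bound on the chance of any false positive is 0.05^(1/60) = 95% in each setting.

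**5. How far P<0.001 is from family-wise control.** Voxel-wise Bonferroni at 5% needs 0.05 / 44,444 = 1.1 × 10⁻⁶ to 0.05 / 66,667 = 7.5 × 10⁻⁷, which is roughly 900 to 1,300 times stricter. A random-field or cluster-level rule would be less strict than this.

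**The case against.** **Silence in a condensed article.** Cluster rules are the kind of detail an article may leave to a fuller plan, and P<0.001 is a plausible cluster-forming threshold. This stands only in part. The article does more than stay silent: it names the test and calls P<0.001 the level of statistical significance. Followed as written, that rule is wrong.

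**The t-test and the design.** A reader might infer that the analysis ignores the pre-intervention scan, or that an independent t-test cannot suit three arms scanned twice. The text does not support that. It does not say which maps enter the test, and the same section refers to changes in MRI data. An independent t-test on change maps for two arms is a valid group-by-time contrast for that pair, and pairwise tests are a usable way to compare three arms. What remains is that the input maps and the contrasts should be named.

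**Correlations with behaviour.** A reader might also infer that false regions feed the correlations between imaging change and behavioural change. The article does not restrict those correlations to significant regions. Only the seed step is documented.

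**Voxels are not regions.** Near certainty is shown for at least one voxel, not for a sizeable region. At the stated 4 mm smoothing, chance clusters were mostly 1 to 2 voxels. This stands and limits the claim. However, ReHo is computed over each voxel and its 26 neighbours, which makes effective smoothness exceed the applied 4 mm by an amount the article does not allow one to calculate.

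**Importance.** The imaging is largely exploratory: Outcome Measures does not list it, and the second hypothesis is not directional. This stands. Seeding from ReHo regions is also a legitimate data-driven choice, because ReHo and seed-based connectivity measure different things.

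**Conclusion.** The point holds as a wrongly stated significance rule for a secondary or exploratory analysis. Under the rule, about 44 to 67 false-positive voxels are expected per null contrast map, and at least one is near certain. These figures assume a 1.2 to 1.8 L search volume. A grey-matter mask would reduce the count in proportion, by one expected false-positive voxel for every 1,000 voxels removed, without providing family-wise control.

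The size of the problem at region level is not fixed by the article. Null clusters of 10 or more voxels ranged from 0% to 83% of maps across 4 to 12 mm smoothness, so the number of chance regions that would become seeds depends on the true smoothness and on an extent rule that is not given. It should not be said that a sizeable false region is near certain.

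The primary inference on the STT is untouched. The change should be made, but it does not threaten the trial's main conclusion.

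**What to change.** In Statistical Analysis:

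1. Keep P<0.001 only as the cluster-forming threshold. Declare significance at cluster-level family-wise P<0.05, adjusted across the pairwise arm contrasts.
2. State that the tests are run on pre-to-post change maps, or on post-intervention maps adjusted for the pre-intervention map, across the three arms, and name the contrasts.

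In Rs-fMRI Data Analysis:

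3. Take as seeds only ReHo regions that survive the corrected threshold, and label the seed-based results exploratory. Pre-specified seeds at the left and right DLPFC are an option, not a required correction.

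This costs analysis wording only; no further scans or patients are needed. The downside is fewer significant regions, and possibly no ReHo region left to seed from, so the plan should say what happens in that case.
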